## 3. Discussion

This protocol presents the rationale and design of a randomized controlled trial to evaluate the effects of a sport-based intervention tailored specifically for pediatric ABI, compared to usual care.

Unlike conventional pediatric rehabilitation focused predominantly on physical impairments, this intervention embraces a multidimensional framework addressing psychosocial well-being and participation—domains often overlooked despite their importance for sustained recovery [32,33].

By adapting sport-based activities to adolescents’ developmental levels and individual interests, the program addresses key determinants of adherence and social engagement in pediatric disability populations [21,22,23,24,33,34]. This child-centered and context-sensitive approach aligns with current best-practice recommendations advocating therapies that extend beyond impairment-focused models [33,34,35]. Moreover, delivering the intervention in a group setting further enhances intrinsic motivation, fosters peer interaction, and supports emotional regulation—well-documented effects in adolescents with neurological and developmental conditions [21,22,23,24].

Similar sport-based interventions have shown positive outcomes in pediatric populations with comparable profiles. In children with cerebral palsy, sport and exercise programs have been associated with improvements in cardiorespiratory fitness, gross motor function, and social participation [22]. Likewise, in developmental disabilities, structured sport-based interventions have demonstrated benefits in physical functioning and behavioral regulation [23,24,36]. These findings support the relevance of sport-based approaches in pediatric ABI, given overlapping functional and psychosocial challenges across these populations.

Different contextual and methodological factors warrant consideration within the scope of this protocol. While the intervention is designed to be flexible and developmentally appropriate, variability in participant age and functional status may affect engagement and the comparability of outcomes. Additionally, external influences such as transport access, family or caregiver involvement, and the level of support from educational or community settings may impact participation. These factors will be monitored and documented to inform the potential adaptation, scalability, and real-world applicability of the intervention.

As a study protocol, this trial introduces a replicable, theory-based intervention that addresses key gaps in pediatric neurorehabilitation literature. It may offer a transferable model to support the transition from clinical rehabilitation to community-based sport participation, encouraging active lifestyles and social inclusion from early recovery. Findings from this trial may have the potential to inform interdisciplinary clinical practice by providing a structured, child-centered approach aligned with family priorities and contextual demands. Ultimately, the results may help to guide clinical decision-making and facilitate the design of long-term engagement strategies that promote sustained participation and well-being in pediatric ABI.

## Figures and Tables

**Figure 1 jcm-14-05970-f001:**
[figure not shown]
Flowchart.

**Table 1 jcm-14-05970-t001:** Eligibility criteria.

Inclusion Criteria	Exclusion Criteria
Be aged <18 years at study entry.	Do not have a completed and signed informed consent form.
Have a medical diagnosis of acquired brain injury in the subacute or chronic stage.	Have medical comorbidities that contraindicate safe exercise (e.g., cardiac or respiratory instability, and uncontrolled seizures).
Be able to understand simple instructions from the program.	Failure to cooperate during the preliminary tests of the program.

**Table 2 jcm-14-05970-t002:** Template for intervention description and replication checklist for the intervention.

Items	Description of Items
Name of the intervention for the experimental/comparison group	Experimental group: sport-based exercise program and usual care sessions. Control group: usual care sessions.
Rationale	
Materials used in the intervention	Experimental group: The program is centered around different sports disciplines, which are adapted to participants’ functional condition, as well as different generic equipment, such as balls, chairs, tables, and platforms, among others.
Intervention procedures	Experimental group: The content of this program is designed around a sport-based framework incorporating motor patterns and task demands from various sports disciplines. It uses a circuit format to promote functional movement, progressive task complexity, and social interaction in small groups tailored by age and functional ability. Group composition will consider motor proficiency, cognitive, and behavioral profiles to balance skill levels and promote peer support. Strategies such as individualized task modification, use of visual and verbal cues, and structured routines will support engagement. Control group: Usual care encompasses a range of therapies (e.g., occupational therapy, physiotherapy, psychological support) provided by the rehabilitation services within the center. Typical frequency is 2–3 sessions per week, mainly individual or small group-based, and does not routinely include sport-based or structured group exercise. Following the post-intervention assessment, participants from this control group can participate in the same program sessions upon request.
Provider	Experimental group: The program will be delivered by a professional with expertise in neurological disorders and adapted physical exercise. Control group: Usual care for this group will be provided by professionals from the rehabilitation center.
Mode of intervention delivery	Experimental group: Presential, group-based sessions (from two to four participants). Control group: Presential, individual sessions.
Setting of intervention	Screening, interventions, and assessments will be conducted at the pediatric hospital, located in Madrid, Spain.
Dosage	Experimental group: Participants from this group will receive a 3-month exercise program which consists of sixteen sessions, 1 h session/day for 2 days/week. Control group: This group will continue with their usual care as usual 2 days/week, over 3 months, and then will be reassessed.
Tailoring	The session’s content will be continuously tailored and adapted by a research team to meet the individual needs and functional levels of each participant, thereby ensuring precise execution and security.
Modifications	Not applicable.
Fidelity assessment	The team responsible for delivering and managing the intervention will conduct a phone follow-up every 2 weeks, as well as other strategies to monitor the adherence and quality of the intervention (session attendance, fidelity checklists). Additionally, this professional will track the progress of participants from the control group during these follow-up calls.

**Table 3 jcm-14-05970-t003:** Schedule of enrolment, interventions, and assessments from the SPIRIT guidelines.

	Study Period		
	Allocation	Baseline	Completion
*ENROLLMENT:*			
Eligibility screen			
Informed Consent			
*INTERVENTIONS:*			
Sports-based exercise + Usual Care			
Usual care			
*ASSESSMENTS:*			
Sociodemographic, anthropometric, and comorbidity data			
Health-related quality of life (PedsQL)			
Physical Activity (GPAQ)			
Participation (CASP)			
Motor functioning (BOT-2)			

Abbreviations: PedsQL, Pediatric Quality of Life Inventory; CASP, Child and Adolescent Scale of Participation; GPAQ, Global Physical Activity Questionnaire; BOT-2, Bruininks–Oseretsky Test of Motor Proficiency.

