## Abstract

**Background/Objectives**: Pediatric acquired brain injury (ABI) often results in persistent challenges that extend beyond motor impairments, affecting quality of life (QoL), social participation, and engagement in physical activity. Given the complexity and chronicity of these outcomes, there is a pressing need for multidimensional interventions grounded in the International Classification of Functioning, Disability and Health (ICF). Sport-based exercise interventions, when developmentally adapted and tailored to individual interests, may promote intrinsic motivation, peer connection, and sustainable engagement—factors especially relevant in pediatric ABI populations, who often experience reduced physical activity and social isolation. However, standardized, replicable protocols specifically tailored to this population remain scarce. This study presents the protocol for a randomized controlled trial evaluating the effects of a 16-week sport-based intervention on QoL, social participation, physical activity engagement, and motor functioning tailored for adolescents with pediatric ABI. **Methods**: Participants will be randomly assigned to an intervention group or a control group receiving usual care. The intervention consists of one weekly 60-minute session, led by trained professionals in adapted physical activity and pediatric neurorehabilitation. It combines sport-based motor skill training, cooperative games, and group activities specifically tailored to each child’s developmental level, motor abilities, and preferences. Outcomes will be assessed at baseline and following the 16-week intervention period, focusing on QoL, participation, physical activity engagement, and motor functioning. **Discussion:** This study introduces a structured, child-centered model that bridges clinical rehabilitation and community-based sport. By integrating motor and psychosocial targets through a group sport-based intervention, it aims to enhance recovery across ICF domains. Findings may inform interdisciplinary practice and support the development of sustainable strategies to promote long-term engagement and well-being in adolescents with ABI.

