### 2.4. Interventions

#### Sport-Based Exercise and Usual Care (Experimental Group)

Participants in the experimental group will engage in a sport-based exercise program in addition to their usual hospital care sessions. The program consists of twice-weekly sessions, each lasting 60 min, over a period of three months. It is structured around a sport-based framework that integrates motor patterns and task demands from a variety of sports disciplines. Sessions are organized in a circuit format that emphasizes functional movement, progressive task complexity, and social interaction within small groups of two to four participants, grouped by age and functional capacity. Each session follows a sample structure including warm-up activities (e.g., dynamic stretching and basic motor skill drills), main circuit stations featuring sports-based tasks such as adapted ball games, obstacle navigation, and coordination drills, and a cool-down with relaxation exercises.

Session content is continuously tailored to each participant’s motor abilities to enable individualized progression, including specific adaptations such as seated or supported activities for children with limited mobility, simplified task demands for those with cognitive or behavioral challenges, and use of assistive devices as needed. Participants’ individual interests and functional goals are identified through baseline assessments and ongoing feedback, which guide activity selection and progression. All sessions are supervised to ensure accuracy and safety.

The Template for Intervention Description and Replication (TIDieR) checklist was used to ensure complete reporting of the intervention (Table 2) [26].

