### 2.7. Study Timeline

Participants will undergo baseline assessments prior to randomization, followed by a second evaluation at the end of the 3-month intervention period (completion). The full study timeline is detailed in Table 3.

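### The abstract, section 2.4 and Table 2 give session frequency, session total and programme length that cannot all be true, so the planned dose and the time of the final assessment are not fixed

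*Protocol article*

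**What the plan says.** The protocol article describes the experimental schedule in three places.

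- **Abstract.** The trial is presented as "evaluating the effects of a 16-week sport-based intervention on QoL" and other outcomes, and "The intervention consists of one weekly 60-minute session".
- **Section 2.4, experimental group.** "The program consists of twice-weekly sessions, each lasting 60 min, over a period of three months". No total number of sessions is given.
- **Table 2 (TIDieR), dosage row.** "Participants from this group will receive a 3-month exercise program which consists of sixteen sessions, 1 h session/day for 2 days/week".

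The time of the final assessment is also given in two ways. The abstract says: "Outcomes will be assessed at baseline and following the 16-week intervention period". Section 2.7 has the baseline visit "followed by a second evaluation at the end of the 3-month intervention period (completion").

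Session length is one hour throughout. The setting, the circuit format and the group size of two to four are described consistently. Table 2 marks modifications as not applicable, and the tailoring it describes concerns the content of sessions, not their number.

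**The concern.** Frequency, duration and total are tied by multiplication: once two are fixed, the third follows. The abstract differs from the other two passages in both frequency and duration. Table 2 states all three quantities, and they do not multiply out.

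Three things depend on the answer:

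- **The treatment being compared.** The planned dose is part of what defines the experimental arm. If it is unclear, neither a positive nor a null result can be attached to a known planned dose. Another centre could not repeat the programme from the article, although the Discussion presents it as replicable. The faulty row is the TIDieR dosage row, which is where a replicating team would look.
- **The endpoint time.** The final assessment applies to both arms, so a shift in its date changes the follow-up of every participant.
- **Adherence.** Table 2 lists attendance among the means of monitoring adherence. A proportion attended needs a fixed number of planned sessions as its denominator.

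**Working it through.** **Inputs**

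| Source | Sessions per week | Duration | Total sessions |
|---|---|---|---|
| Abstract | 1 | 16 weeks | not stated |
| Section 2.4 | 2 | 3 months | not stated |
| Table 2, dosage | 2 | 3 months | 16 |

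Session length is 1 hour in all three, so hours equal sessions.

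**Formula.** Total sessions = sessions per week × weeks. The article does not convert three months into weeks, so I use a range: 12 weeks (4-week months) to 13 weeks (calendar: 365.25 / 12 × 3 / 7 = 13.04).

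**Can Table 2's own figure of 16 be reproduced?**

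- 2 per week × 12 weeks = 24
- 2 per week × 13 weeks = 26
- 1 per week × 12 to 13 weeks = 12 to 13
- 1 per week × 16 weeks = 16, but this is neither two days a week nor three months
- 2 per week × 8 weeks = 16, but this is not three months

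No combination gives 16 with both two days a week and three months. Working back, 16 / 2 = 8 weeks. Spread over three months, 16 / 12 = 1.33 and 16 / 13 = 1.23 sessions per week, not 2.

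**What each passage implies**

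- Abstract: 1 × 16 = 16 sessions, 16 hours.
- Section 2.4: 2 × 12 to 2 × 13 = 24 to 26 sessions, 24 to 26 hours.
- Table 2: 16 sessions if its total is kept; 24 to 26 if its frequency and duration are kept.

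**Size of the difference**

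- Total contact: 24 / 16 = 1.50 and 26 / 16 = 1.63, so 50% to 63% more, or 8 to 10 additional hours.
- Weekly exposure: 1 hour against 2 hours.
- Final assessment: 16 − 13 = 3 weeks to 16 − 12 = 4 weeks apart.
- Attendance for someone who comes to 16 sessions: 16 / 16 = 100%, against 16 / 26 = 62% to 16 / 24 = 67%.

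**The case against.** The strongest reply is that the disagreement is narrower than it looks. Section 2.4 and Table 2 agree on two sessions a week, one hour each, over three months. Section 2.7 and the control entry in the dosage row also say three months. On this reading there are two local errors, the abstract's schedule and the word sixteen in Table 2, and the rest of the treatment is well described. The figures of 8 weeks and 24 to 26 sessions appear nowhere in the article; they are derived and assume sessions every week without a break. The main analysis in section 2.10 is by intention to treat, and no per-protocol set or attendance threshold is stated, so the attendance denominator affects only descriptive reporting. The delivered dose could still be reported from attendance records, and the sample size does not depend on the dose.

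Much of this is fair, and it limits the claim: what is unsettled is the schedule and the total, not the content of the programme. It does not remove the contradiction. With the abstract corrected, Table 2 would still state three figures that cannot hold together, and its total would still conflict with section 2.4. Sixteen sessions with gaps inside a three-month window would be possible, but the article does not say so, and that would fit neither the abstract nor an uninterrupted twice-weekly programme. Agreement of several passages on three months does not show which total is meant. Recording what was delivered does not establish what was planned. Condensing a full protocol into an article explains omissions, but not figures that are present and incompatible.

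**Conclusion.** The concern holds. The three descriptions of the schedule cannot all be true, and the dosage row of Table 2 cannot be true on its own terms. Planned contact is 16 hours or 24 to 26 hours, weekly exposure is 1 or 2 hours, and the final assessment is at 16 weeks or about 3 to 4 weeks earlier. Attendance at 16 sessions is complete or 62% to 67% complete, depending on the passage followed.

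These sizes rest on two assumptions: three months means 12 to 13 weeks, and the twice-weekly sessions run without planned breaks. The internal contradiction in Table 2 does not depend on the choice between 12 and 13 weeks. The sample size and the intention-to-treat comparison are formally unaffected. What is affected is the definition of the experimental arm, the time at which both arms are measured, and any statement about adherence. The article does not show which schedule is intended. This should be corrected because it governs what participants receive and when they are assessed.

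**What to change.** Reconcile the abstract, section 2.4 (experimental group), section 2.7 and the dosage row of Table 2 so that they give one frequency, one total number of sessions and one duration that multiply out. If planned breaks explain the total, say so and give their length. State the final assessment as a number of weeks from a named starting point, the same in both arms. While doing this, also clear up the control-group paragraph of section 2.4, which places the post-intervention assessment three months after the intervention and so, read literally, differs from section 2.7. Name the agreed total as the denominator for attendance and fidelity.

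The choice of schedule belongs to the investigators. It should be settled before the first participant starts. The article gives no start date, so if enrolment has begun, the schedule actually used should be documented with its dates.

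The cost is a correction of wording, plus alignment of the registry record and consent text if they carry a different version; neither was available for this review. No change to the sample size or the analysis follows from it.

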## Data Availability

The datasets are available from the corresponding author on request.
